### Quality control

2.27

To ensure the research quality and data validity, we will conduct unified and standardized training for the study researchers, formulate clinical research SOPs, and ensure that the clinical research consistently follows the operating procedures. Regular monitoring will be used to ensure the study's authenticity and reliability.

### Statistical analysis

2.28

A third-party medical statistics professional will perform statistical analysis. After the subject research plan and case report form are reviewed by experts, a third party will formulate a statistical analysis plan and determine the statistical software to use.

### Specific statistical methods

2.29

#### Statistical analysis of general data, behavioral tests, and blood biomarkers

2.29.1

The metrological data of the measured data were expressed as “mean ± standard deviation,” and the normality test was carried out. If all data were in line with normal distribution (*P* > .05), *χ*^2^ test was used for counting data, *t* test was used for measurement data, double-sample *t* test was used for comparison between the 2 groups, and paired-sample *t* test was used for comparison within the group. The test level was *P* = .05, if *P* < .05 indicated statistically significant difference. The above statistical work is analyzed and processed by specialized statisticians using SPSS25.0 statistical software (SPSS Inc, Chicago, IL).

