### Trial design

2.2

This is an outcome assessor- and data analyst-blinded, partial randomized controlled trial conducted at the Second Affiliated Hospital of Heilongjiang University of Chinese Medicine from January 1, 2021 to December 31, 2023. A total of 80 subjects who met the inclusion criteria including 25 healthy volunteers, 25 T2DM patients with normal cognitive function, and 30 patients with VCI combined with T2DM were recruited into the study. First, they were scanned by fMRI, through the calculation and analysis of VBM indexes, the changes in hippocampal volume and function in the 3 groups of patients were compared to determine the difference between type 2 diabetes patients and healthy volunteers, correlation between hippocampal structural and functional changes in patients with normal cognitive T2DM and VCI patients with T2DM. Then, 30 VCI patients with T2DM were randomly divided into the experimental group and the control group, the control group was given routine drug therapy to control blood glucose and improve cognitive function, the experimental group was given acupuncture-rehabilitation therapy on the basis of the control group. The primary outcomes were obtained by VBM calculation and serum biomarkers (SOD, MDA, BDNF) detection, and the secondary outcome indexes were assessed by neuropsychological scales such as Montreal Cognitive Assessment (MoCA), Wechsler Memory Scale IV edition (WMS-IV), FIM, among others. Serum biological indicators and neuropsychological scale will be conducted before treatment, as well as 4 weeks, 8 weeks, and 12 weeks after treatment respectively, fMRI scan will be conducted before treatment and 12 weeks after treatment respectively, to observe the intervention effect of acupuncture-rehabilitation therapy on cognitive function of VCI patients with T2DM. Figure 1 and Table 1*present the technology roadmap and clinical observation flow charts, respectively.*

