### Sample size

2.5

We will conduct this study using a partial randomized controlled trial design, and the main observed outcome will be improvements in VCI patients with T2DM cognitive function. Our previous clinical observation found that 4 weeks of acupuncture-rehabilitation therapy treatment and routine drug therapy can improve scores on the MoCA scale by 3.13 ± 0.75 and 1.53 ± 0.33 points, respectively.^[5]^ Use PASS15.0 software to calculate, with the significance test level set at 0.05 and the test power at 0.9, the required sample size was 13 subjects for each group. Considering a dropout rate of 15%, a total of 30 subjects needed to be enrolled in VCI group with T2DM (15 participants per group). Then the Healthy volunteers group and T2DM group with normal cognitive function group were matched with the corresponding patient volume (25 participants per group). Therefore, a total of 80 subjects were included in this study.

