### Outcome measures

2.21

All participants will be were evaluated for serum biological indicators and neuropsychological scales before treatment, 4 weeks of treatment, 8 weeks of treatment, and 12 weeks after treatment. fMRI scans were performed before treatment and 12 weeks after treatment. All treatment evaluations will be conducted by researchers who will be blinded to the treatment allocation.

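### Section 2.29.1 lets the tests for the serum and scale outcomes depend on whether all data pass a normality test, so those tests are settled only after the outcome data are seen.

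*Protocol article*

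**What the plan says.** Section 2.29.1 of the protocol article covers general data, behavioural tests and blood biomarkers. After a normality test, it sets the condition "If all data were in line with normal distribution" with a pass mark of P > .05. Three procedures follow from that condition: the chi-square test for counts, the two-sample t test ("test was used for comparison between the 2 groups"), and the paired t test within groups.

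The outcomes under this rule are listed in Section 2.2. Three are primary: "The primary outcomes were obtained by VBM calculation and serum biomarkers (SOD, MDA, BDNF) detection". The secondary ones are "Montreal Cognitive Assessment (MoCA), Wechsler Memory Scale IV edition (WMS-IV), FIM". Section 2.21 schedules the serum measures and scales "before treatment, 4 weeks of treatment, 8 weeks of treatment, and 12 weeks after treatment". Section 2.5 plans "15 participants per group" in the randomised part.

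Section 2.29.2 treats the imaging data differently. The two-sample and paired t tests for VBM, ReHo and FC carry no normality condition.

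**The concern.** A comparison between randomised arms should be fixed before outcome data are inspected. Here a result computed from those data decides whether the stated test applies to three primary outcomes and to MoCA, the outcome used for sizing. The wording is also hard to apply. It speaks of all data together, so one failure in one variable could, read literally, set aside the t test for every other variable. It also puts a test for counts under a condition that has no meaning for counts.

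A normality test also says nothing about unequal spread. The protocol's own MoCA figures show it: two treatments that "can improve scores on the MoCA scale by 3.13 ± 0.75 and 1.53 ± 0.33 points, respectively". If the arms also end up unequal in size, an ordinary pooled t test can miss its nominal level even when every normality test is passed.

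**Working it through.** **Plan's own figure.** The protocol gives no probability for the normality condition and no number of normality tests, so there is nothing to reproduce on that point.

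**Inputs.** From Sections 2.2, 2.5 and 2.21: 6 measures (one total score per scale), 4 visits, 2 arms, 15 per arm. From Section 2.29.1: pass if P > .05, which is a 5% false rejection rate per test on truly normal data. Assumption: the unit of testing. Tested per arm, all six measures give 6 × 4 × 2 = 48 tests. WMS-IV indices, general data, paired differences and the non-randomised groups would add to this.

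**Step 1: chance that the condition fails when all data are normal.** For k independent tests it is 1 − 0.95^k.

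| Reading | k | Chance of failure |
|---|---|---|
| One measure, one visit, two arms | 2 | 9.8% |
| One measure, four visits, two arms | 8 | 33.7% |
| Serum measures only by arm, or all six with arms pooled | 24 | 70.8% |
| All six measures by arm | 48 | 91.5% |

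The tests are not independent. Shapiro-Wilk simulations with 13 or 15 per arm and 48 tests gave 90% to 92% at correlations of 0.5 over time and 0.2 to 0.3 between measures. They gave about 90% at 0.7 and 0.3, and 83% to 85% at 0.9 and 0.5. With 24 tests the simulated range was 68% to 72%.

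**Step 2: does the screen itself damage the error rate?** The screen was simulated variable by variable at 15:15: pooled t if both arms pass, otherwise Mann-Whitney (an assumed fallback). Type I error was about 4.6% to 5.3% for normal and log-normal data. The screen is also weak: 15 values from a log-normal with log-SD 0.4 or 0.6 are flagged only about 27% or 50% of the time. But the pooled t test on such data had 4.4% to 4.8% error with equal arms, so missed skew does not inflate it.

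**Step 3: unequal spread.** The variance ratio from Section 2.5 is 0.75² / 0.33² = 0.5625 / 0.1089 = 5.2. Compare the true variance of the difference, 0.5625/n1 + 0.1089/n2, with the expected pooled estimate, sp²(1/n1 + 1/n2), where n1 is the arm with SD 0.75:

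- 15:15: true 0.0448, pooled 0.0448; no bias.
- 12:15: true 0.0541; sp² = (11 × 0.5625 + 14 × 0.1089)/25 = 0.3085, pooled 0.3085 × 0.15 = 0.0463. The standard error is about 8% too small, since √(0.0463/0.0541) = 0.92.
- 10:15: true 0.0635; sp² = (9 × 0.5625 + 14 × 0.1089)/23 = 0.2864, pooled 0.0477. The standard error is about 13% too small.
- 15:12: true 0.0466; sp² = (14 × 0.5625 + 11 × 0.1089)/25 = 0.3629, pooled 0.0544. The standard error is about 8% too large.

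Simulated two-sided type I error at nominal 5% (ranges are across separate runs):

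| n1:n2 | Pooled t |
|---|---|
| 15:15 | 5.3% to 5.4% |
| 12:15 | 7.2% to 7.5% |
| 10:15 | 9.2% to 9.5% |
| 15:12 | 3.8% to 3.9% |

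The Welch test stayed between 4.9% and 5.3% throughout.

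**The case against.** The strongest reply is that a translated, condensed article probably means variable by variable: a measure that looks normal gets a t test. A statistician would hardly drop the t test for MoCA because FIM failed at one visit. This is fair. A reader might infer that the stated analysis is unreachable about nine times in ten. That figure needs the literal reading and a count of 48 that the document does not give, so it cannot stand as a fact about the plan. What survives is that even the mildest reading leaves the choice of test to the outcome data.

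A reader might also infer that the trial's whole primary analysis is affected. It is not, because VBM is a primary outcome and its tests are fixed in Section 2.29.2.

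Nor does the material show that the normality screen inflates type I error; with equal arms it hardly does. The larger figures come from unequal variance together with unequal loss. They assume a pooled test, which Section 2.29.1 does not specify. The 10:15 case means 5 of 15 (33%) lost in one arm and none in the other, against a planned 15%. The SDs are four-week MoCA changes from an earlier study and say nothing about SOD, MDA or BDNF. They are also uncertain evidence for this trial: with a root-mean-square SD of 0.579 and a difference of 1.60, the normal approximation gives 2 × (1.96 + 1.282)² × 0.579² / 1.60² = 2.8, or 3 per arm, not the stated 13. That is a separate matter.

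Finally, Section 2.28 leaves a statistical analysis plan to a third party, which may name a fallback. The absence of one here is therefore not the point. The trigger that is written here would depend on outcome data whatever fallback is named. Blinding of the analyst (Section 2.17) limits deliberate choice but does not remove that dependence.

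**Conclusion.** The point holds in limited form. Section 2.29.1 states a data-dependent rule for the three serum primary outcomes and the three scales, and it wrongly extends it to counts. How often the condition fails with normal data depends on an unstated number of tests, from about 10% for a single comparison to 83% to 92% for the assumed 48. The cost in type I error from the screen itself is small with equal arms. The error that it leaves unaddressed is negligible at 15:15. It is moderate at 12:15 if the smaller arm has the larger SD, and conservative in the reverse case. Those figures assume SDs like the MoCA ones and a pooled test. Unequal arms are plausible, since Section 2.5 expects 15% dropout and Section 2.13 removes withdrawals and violators. This is a minor to moderate correction.

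**What to change.** Delete the normality condition from Section 2.29.1 and give the chi-square test for counts its own sentence. For each serum and scale outcome, name one between-arm test in advance. The better choice is a comparison adjusted for the baseline value, which is already collected, with unequal-variance standard errors. If t tests are kept, use the Welch two-sample t test. A pre-stated rank-sum result for SOD, MDA and BDNF is an optional sensitivity analysis.

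The change is to wording only. No added data are needed, and SPSS, the software named in the section, prints the unequal-variance t test by default. The downside is a very small loss of power when the variances are in fact equal. The text should be settled before the outcome data are examined.

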#### Statistical processing and result presentation of brain function data

2.29.2

Statistical analysis is carried out by using DPASFA, SPM12, Xjview, Rest, and other software based on MATLAB platform.

The values of VBM, ReHo, and FC of healthy volunteers, T2DM cognitive normal group, and VCI group with T2DM were analyzed by ANOVA, with sex, age and years of education as covariates. The test level was set to: cluster level *P* < .05 (FWE or FDR correction). If *P* < .05 and could at least pass the FDR correction, there was a significant difference between the 2 groups of patients and healthy volunteers, which was statistically significant.

In the VCI group with T2DM, the data of VBM, ReHo, and FC in the experimental group and the control group were compared by double-sample *t* test. Paired-sample *t* test was used for intra-group comparison between the 2 groups before and after treatment. The test level was set as: cluster level *P* < .05 (FWE or FDR correction). If *P* < .05 and could at least pass the FDR correction, it was considered that there was a significant difference between the experimental group and the control group, which was statistically significant.

The statistical results were presented by Xjview and Mricron software.

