#### Inclusion criteria of VCI patients with T2DM

2.9.1

1.It conforms to the diagnostic points of T2DM and VCI, and has been confirmed to have suffered from ischemic or hemorrhagic stroke by CT or MRI.2.With cognitive impairment, the score of the Montreal Cognitive Assessment scale (MoCA-Beijing version) is <26 (if the length of education is <12 years, one point is added to the test results to correct the cultural influence). The overall cognitive function is fully preserved, and the score of Mini Mental State scale (MMSE) ≥24. It did not meet the diagnostic criteria of dementia in the fourth edition of the American Diagnostic and Statistical Manual of Mental Disorders, with a clinical dementia scale (CDR) score of 0.5. Activities of daily living (ADL) were not significantly impaired, and the IADL score ≥16.3.Can cooperate to complete fMRI scan.4.The course of stroke ranges from 3 to 12 months.5.The range of age from 50 to 60 years old, right-handedness.6.No verbal language dysfunction.7.Have not received acupuncture or rehabilitation treatment in the past three months.8.Not accompanied by depression, mental symptoms and infectious diseases.9.The following categories of drugs were not used within 30 days before screening for cognitive impairment: drugs for the treatment of Alzheimer disease or dementia, anti-Parkinson disease drugs, short-acting antianxiety agents, nerve sedatives or analgesics, antiepileptic drugs, hormones, drugs with significant cholinergic or anticholinergic side effects.

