### Inclusion criteria of healthy volunteers

2.11

1.Do not meet the diagnostic criteria for diabetes, and stroke is excluded as confirmed by CT or MRI.2.Cognitive function is normal, MoCA score ≥26 points (if the length of education is <12 years, 1 point is added to the test results to correct the cultural influence). MMSE score ≥24.CDR score is 0.IADL score ≥16.3.Can cooperate to complete fMRI scan.4.The range of age from 50 to 60 years’ old, right-handedness.5.Diseases without brain trauma, drug and alcohol dependence that may affect the structure and function of the brain, not accompanied by depression, mental symptoms and other diseases.

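### The non-randomised three-group model for ReHo and FC adjusts for sex, age and education but has no head-motion term, so motion left after preprocessing could be read as a difference in brain function

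*Protocol article*

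**What the plan says.** Section 2.29.2 sets out the group-level imaging analysis. "The values of VBM, ReHo, and FC of healthy volunteers, T2DM cognitive normal group, and VCI group with T2DM" go into one model, and they "were analyzed by ANOVA, with sex, age and years of education as covariates". No other covariate is named. A result counts as significant at cluster level P < .05 if it "could at least pass the FDR correction".

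Section 2.2 (Trial design) gives the group sizes as "25 healthy volunteers, 25 T2DM patients with normal cognitive function, and 30 patients with VCI combined with T2DM" and the purpose of the first stage: "the changes in hippocampal volume and function in the 3 groups of patients were compared".

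The groups differ by design. A VCI patient qualifies only if he or she "has been confirmed to have suffered from ischemic or hemorrhagic stroke by CT or MRI" (section 2.9.1). For healthy volunteers, "stroke is excluded as confirmed by CT or MRI" (section 2.11), and section 2.10 also excludes stroke in the T2DM patients with normal cognition. Under section 2.16, only the VCI patients are randomised; the other two groups are filled in order of attendance.

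The article does not mention head motion as a covariate, as a nuisance regressor or as a limit on scan quality. The only scan-related eligibility rules concern being able to complete the scan (sections 2.9.1, 2.10, 2.11 and item 8 of 2.12).

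**The concern.** One covariate list serves a structural measure (VBM) and two measures computed from the functional signal (ReHo and FC). Sex, age and education are sensible for all three, but none of them deals with a disturbance specific to functional scans. ReHo and FC describe how signals vary together over the length of a scan, so it is reasonable to expect that movement during the scan can alter them.

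In a non-randomised comparison, a variable that differs between groups and affects the outcome biases the group contrast unless it is removed earlier or adjusted for. Patients 3 to 12 months after a stroke may move differently from people without one. A subject who completes the scan but moves more stays in the analysis.

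At stake is the functional half of the first-stage comparison. Section 2.23 describes VBM as a technique for brain structure, so among the measures in 2.29.2 any statement about hippocampal function across the three groups has to come from ReHo and FC. The multiplicity correction in 2.29.2 limits chance findings over many voxels. It does not protect against a systematic shift.

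**Working it through.** The plan states no figure on motion, so there is nothing to reproduce. The check asks how much an omitted motion term could matter at the planned sample sizes.

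**Inputs from the article.** Group sizes 25, 25 and 30 (section 2.2); three covariates and a 5% level (section 2.29.2).

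**Inputs assumed.** *d* is the difference in mean motion between VCI patients and a stroke-free group, in SD units. *r* is the within-group correlation between motion and the imaging measure that remains after preprocessing. The article gives neither. The range used is *d* = 0.3 to 0.8 and *r* = 0.2 to 0.4, with a linear motion effect and no true group difference.

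**Step 1: bias.** Omitting motion shifts the group contrast by *r* × *d* SD of the measure. Smallest: 0.2 × 0.3 = 0.06 SD. Largest: 0.4 × 0.8 = 0.32 SD.

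**Step 2: false-positive rate of one two-group test, 25 v 30.** The noncentrality is *r* × *d* × √(25 × 30 / 55) = *r* × *d* × 3.693, with 53 degrees of freedom and a two-sided 5% critical value of 2.006.

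| *d* | *r* | Bias (SD) | Noncentrality | Rate |
|---|---|---|---|---|
| 0.3 | 0.2 | 0.06 | 0.22 | 5.5% |
| 0.5 | 0.3 | 0.15 | 0.55 | 8.5% |
| 0.8 | 0.3 | 0.24 | 0.89 | 14.0% |
| 0.8 | 0.4 | 0.32 | 1.18 | 21.3% |

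Simulation with 20,000 replicates agrees for the last three rows (8.2%, 13.9% and 21.4%). With motion in the model the rates are 4.8%, 5.2% and 5.1%.

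**Step 3: the stated model.** A separate simulation used all three groups (25/25/30), three covariates and the overall group F-test, with 4,000 runs per setting. Only the VCI group was shifted.

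| *d* | *r* | Without motion | With motion |
|---|---|---|---|
| 0 | 0.3 | 4.9% | 4.9% |
| 0.3 | 0.3 | 5.6% | 4.6% |
| 0.5 | 0.3 | 7.7% | 4.7% |
| 0.8 | 0.1 | 5.5% | 4.7% |
| 0.8 | 0.3 | 12.8% | 5.2% |

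If the groups move alike, or if little motion effect survives preprocessing, nothing is lost by the present model. If both conditions fail, the rate can more than double.

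**Step 4: price of adjustment.** Tying motion to group widens the standard error of the 25 v 30 contrast by √(1 + *pqd*²), where *pq* = (25/55) × (30/55) = 0.248. At *d* = 0.3 this is √1.022 = 1.01; at *d* = 0.8 it is √1.159 = 1.08. The adjustment also removes residual variance, a factor of √(1 − *r*²), which is √0.84 = 0.92 at *r* = 0.4. The net loss is therefore at most a few per cent.

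**The case against.** The strongest reply is that this is a condensed article. Section 2.29.2 names software and group-level tests but no preprocessing, and section 2.28 says that an outside statistician will write an analysis plan, which is not shown. Motion is commonly handled at subject level, by realignment, motion regressors or scan rejection. A reader might infer from the article's silence that motion is uncontrolled, and that inference is not supported. The narrower point stands: the article does state the group-level covariates, and whatever motion effect preprocessing leaves passes into a model with no term for it.

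A reader might also take it as established that stroke patients move more and that this alters both measures. The documents contain no motion data. Eligibility also narrows the contrast: every group is aged 50 to 60, has MMSE of at least 24 and must be able to complete the scan, and the VCI patients have CDR 0.5. The case therefore rests on what may happen.

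A third tempting extension is to the comparison of the two VCI arms, where "the data of VBM, ReHo, and FC in the experimental group and the control group were compared by double-sample" t test without covariates. That comparison is randomised, 15 v 15, so baseline motion is balanced in expectation. Change in motion is measured after randomisation and treatment could affect it, so adjusting for it could introduce a problem of its own.

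Finally, ReHo and FC are in neither the primary nor the secondary outcome list (sections 2.23 and 2.24), and section 2.2 describes the three-group comparison as made through VBM indexes. This limits the importance of the point. It does not remove it, because 2.29.2 tests ReHo and FC across the groups and declares differences on them.

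**Conclusion.** The point holds for one model only: the baseline three-group comparison of ReHo and FC. Its stated covariates omit head motion, the groups are not randomised, and they differ in stroke by design. A residual motion difference could be reported as a difference in brain function.

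The size cannot be known from the documents. Under assumed motion differences of 0.3 to 0.8 SD and residual correlations of 0.2 to 0.4, the bias is 0.06 to 0.32 SD and the single-test false-positive rate is about 5.5% to 21%. A reader might take those percentages as the error rate of the planned analysis. They are not: they apply to one test at 5% and not to whole-brain inference with cluster-level correction. With no motion difference, or a residual correlation of 0.1, there is essentially no inflation.

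No randomised conclusion, VBM result or listed primary or secondary outcome is put in doubt. This is a cheap improvement to a stated model and does not show that the trial's functional findings will be wrong.

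**What to change.** In section 2.29.2, add each subject's mean framewise displacement to the covariates of the three-group ReHo and FC model, alongside sex, age and years of education. Leave the VBM model as it is, and do not add a change-in-motion covariate to the comparison of the randomised arms.

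The change takes one sentence and no new data, since the displacement values can be obtained by realigning the scans already planned. It uses one degree of freedom among 80 subjects. If motion is tied to group, the adjusted contrast is slightly less precise: by about 1% to 8% in standard error over the assumed range, before allowing for the residual variance that the covariate removes.

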### Inclusion criteria for patients with normal cognitive function in T2DM

2.10

1.Meet the diagnostic criteria of T2DM, and was confirmed by CT or MRI to exclude stroke.2.Cognitive function is normal, MoCA score ≥26 points (if the length of education is <12 years, one point is added to the test results to correct the cultural influence). MMSE score ≥24.CDR score is 0.IADL score ≥16.3.Can cooperate to complete fMRI scan.4.The range of age from 50 to 60 years’ old, right-handedness.5.No verbal language dysfunction.6.Have not received acupuncture or rehabilitation treatment in the past 3 months.7.Not accompanied by depression, mental symptoms, and infectious diseases.8.The following categories of drugs were not used within 30 days before screening for cognitive impairment: drugs for the treatment of Alzheimer disease or dementia, anti-Parkinson disease drugs, short-acting antianxiety agents, nerve sedatives or analgesics, antiepileptic drugs, hormones, drugs with significant cholinergic or anticholinergic side effects.

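### The three-group imaging ANOVA carries a conclusion about patients versus healthy volunteers that an omnibus test cannot support, and no contrast is stated for the two comparisons the trial asks about

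*Protocol article*

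**What the plan says.** Section 2.29.2 fixes the imaging analysis of the three baseline groups: "The values of VBM, ReHo, and FC of healthy volunteers, T2DM cognitive normal group, and VCI group with T2DM were analyzed by ANOVA", adjusted "with sex, age and years of education as covariates". The threshold is 5% at cluster level with FWE or FDR correction. The section then attaches a conclusion to a significant result, namely that "there was a significant difference between the 2 groups of patients and healthy volunteers, which was statistically significant".

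The questions this analysis serves are in the Abstract (Methods/Design) and section 2.2. One aim is "to determine the difference between type 2 diabetes patients and healthy volunteers". The other sets cognitively normal T2DM patients against VCI patients with T2DM. Group sizes are 25, 25 and 30.

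No other test in the article covers these comparisons. The two-sample and paired t tests in 2.29.2 apply inside the randomised VCI group. Those in 2.29.1 apply to general data, behavioural tests and blood biomarkers. Section 2.28 leaves a statistical analysis plan to a third party.

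**The concern.** The F test rejects when any one of the three means departs from the others. It rejects when the VCI group alone is different, and it then says nothing about diabetes without cognitive impairment. Under the stated rule that result would be reported as a difference between the patients and the healthy volunteers. The FWE or FDR correction does not help, because it works over voxels or clusters and not over pairs of groups. The stated conclusion also does not mention the second question at all.

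A pattern in which only the VCI group differs cannot be dismissed, because stroke status coincides with that group. A VCI patient "has been confirmed to have suffered from ischemic or hemorrhagic stroke by CT or MRI", whereas a cognitively normal T2DM patient "was confirmed by CT or MRI to exclude stroke"; section 2.11 excludes stroke in healthy volunteers as well.

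VBM is listed among the primary outcomes, and 50 of the 80 participants (25 + 25) are recruited as comparison groups. At stake is whether the baseline imaging can properly answer either question for which those 50 people are scanned.

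**Working it through.** The plan states no figure for this analysis, so there is none to reproduce. The check asks how often the F test would be significant when the stated conclusion is false for T2DM.

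**Inputs.** Group sizes 25, 25 and 30 (section 2.2). Three covariates (section 2.29.2), so the error degrees of freedom are 80 − 3 − 3 = 74. Level 0.05. The standardised difference d is an assumption, because the documents give no imaging effect size.

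**Scenario 1: T2DM equals healthy, VCI differs by d.** The noncentrality is λ = [30 × (25 + 25) / 80] × d² = 18.75 d². The rejection probability is P(F′ > 3.12), where F′ is noncentral F on 2 and 74 degrees of freedom.

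| d (SD) | λ | P(F test significant) |
|---|---|---|
| 0.3 | 1.69 | 0.19 |
| 0.5 | 4.69 | 0.46 |
| 0.8 | 12.00 | 0.87 |
| 1.0 | 18.75 | 0.97 |
| 1.2 | 27.00 | 0.997 |

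**Direct contrast under the same scenario.** In 20,000 simulated trials without covariates, the proportion with both a significant F test and a significant healthy-versus-T2DM contrast was 0.051 at d = 0.8 and 0.048 at d = 1.0.

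**Scenario 2: the sentence is read as pooled patients versus healthy.** Put T2DM at +d/2, VCI at −d/2 and healthy at 0, so that the simple average of the two patient means equals healthy. The weighted grand mean is (25 × d/2 − 30 × d/2) / 80 = −0.03125 d. Then λ = 25(0.03125d)² + 25(0.53125d)² + 30(0.46875d)² = 13.67 d². At d = 0.8, λ = 8.75 and the F test rejects with probability 0.74; at d = 1.0, λ = 13.67 and it rejects with probability 0.91. The pooled reading is not supported by the F test either.

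**Effect of a stricter threshold.** Cluster-level correction is not modelled. As a rough indication, scenario 1 at P < .001 (critical F 7.59) gives 0.07, 0.40 and 0.71 at d = 0.5, 0.8 and 1.0. The rates fall but the inference stays invalid.

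**Power of the two named contrasts.** The noncentrality is d / √(1/n₁ + 1/n₂). At d = 0.8 that is 0.8/√(2/25) = 2.83 for healthy versus T2DM and 0.8/√(1/25 + 1/30) = 2.95 for T2DM versus VCI.

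| Contrast | d (SD) | Level 0.05 | Level 0.025 |
|---|---|---|---|
| Healthy vs T2DM | 0.8 | 0.80 | 0.71 |
| Healthy vs T2DM | 1.0 | 0.94 | 0.89 |
| T2DM vs VCI with T2DM | 0.8 | 0.83 | 0.75 |
| T2DM vs VCI with T2DM | 1.0 | 0.95 | 0.92 |

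**The case against.** The strongest reply has two parts. First, the English is loose, and the sentence may mean only that the three groups differ among themselves, which an F test does support. Second, follow-up contrasts are often left to the statistical analysis plan that section 2.28 promises, so their absence from an article proves little.

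Both parts limit the point. A reader might infer that the two comparisons will never be tested; the documents show only that no test is stated. On the milder translation the sentence is not false, but neither question is then answered by the stated rule. On its ordinary reading, the sentence fixes a conclusion that the test does not deliver. That is a stated rule, not a detail left for later.

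Three further inferences go too far:

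- **Head size.** The covariate list ("analyzed by ANOVA, with sex, age and years of education as covariates") has no intracranial volume, which invites the claim that VBM is unadjusted for head size. Preprocessing is not described, so scaling at that stage cannot be excluded.
- **Stroke.** The T2DM-versus-VCI comparison carries stroke along with cognition, but the protocol never says that it isolates cognition, and vascular injury is part of how it defines VCI. This calls for careful wording only.
- **The 87%.** This is not a property of the planned analysis. It assumes that T2DM equals healthy exactly and that VCI differs by 0.8 SD, on one measure without cluster correction. The Discussion itself cites a VBM study finding smaller regional volumes in T2DM, so that scenario should not be called the likeliest.

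**Conclusion.** The point holds as a should-fix. The conclusion in section 2.29.2 does not follow from the test to which it is attached, and the article states no imaging contrast for either of its two baseline questions. If T2DM and healthy volunteers are alike and only the VCI group differs, a significant F test would arise about 46% to 97% of the time for differences of 0.5 to 1.0 SD, against about 5% for a direct T2DM-versus-healthy contrast. These rates rest on assumed effects and a single normally distributed measure tested at 5%. They illustrate the fault and do not predict the trial.

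A reader might infer that the treatment result is compromised. It is not: the experimental and control arms have their own direct two-sample test, which this does not touch. The affected analysis is the non-randomised baseline comparison, which is why it ranks below a must-fix.

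**What to change.** Replace the conclusion sentence in section 2.29.2 with two pre-specified contrasts in the same covariate-adjusted model: healthy versus cognitively normal T2DM, and cognitively normal T2DM versus VCI with T2DM. Keep the cluster-level correction within each contrast. Control multiplicity across contrasts either by testing them only after a significant F test, which is sufficient with three groups, or by a two-contrast correction. Claim a difference only for a contrast that is itself significant.

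Two secondary changes are worth making at the same time. For VBM only, add total intracranial volume as a covariate unless preprocessing already scales for head size. Describe the second contrast as VCI with stroke and T2DM versus stroke-free T2DM.

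The cost is a change of wording in the article and the analysis plan, with no new participants or scans. If the two-contrast correction is chosen, some power is lost: at 0.8 SD, healthy versus T2DM falls from 0.80 to 0.71. The reported conclusions will also be narrower.
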